### Assignment

We will attempt to emulate random allocation or randomization by adjusting for dietary intakes in the year before the intervention, as well as adjusting for covariates at the start of the study. Covariates were identified using the causal diagrams depicted in Figure 1, based on background knowledge of the relationship between the hypothetical lifestyle intervention and outcomes.

Dietary components that are the foundation for healthy eating in CFG include intakes of vegetables and fruits, whole grains, protein foods (plant- and animal-based protein foods, milk, and plant-based beverages with protein), and unsaturated oils and fats [1].

Covariates, including age at baseline, biological sex, region, education, living alone, smoking and drinking (alcohol) habits, major chronic diseases (ie, hypertension, diabetes, cancer, and heart disease), the number of medications, supplement use (eg, vitamins and minerals), and height and weight, are as follows:

*Z*, baseline covariates: age, sex, region, education, history of smoking, height, and former cancer history*P*, previous exposure (ie, exposure of time-varying intervention before baseline): dietary habits before baseline*L*, (time-varying) covariates: weight, number of medications, supplement use, living alone, major chronic diseases (eg, hypertension, diabetes, cancer, and heart disease), and smoking and alcohol habits*X*, (time-varying) treatment: diet and physical activity habits*Y*, end of follow-up outcome: muscle health, general health, and cognitive health

Contrary to dietary habits, data on physical activity habits before baseline were not collected in NuAge. In this case, the potential effect of previous physical activity habits will not be accounted for in the models that aim to emulate the sustained physical activity intervention strategy. For the models emulating the sustained diet intervention strategy only, physical activity habits during the study will be used as a covariate, hence mitigating the confounding of previous physical activity, at least to some extent.

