### Study Design and Sample

Data from the NuAge prospective cohort will be used to emulate the target trial [25]. The NuAge cohort comprised 1753 generally healthy community-dwelling adults aged 67 to 84 years at baseline and followed for 3 years. The baseline and each annual follow-up evaluation included a comprehensive assessment of sociodemographic data, diet, physical activity, functional status, as well as physical and mental health status [25].

The NuAge sample is relevant to our research question. The target population of CFG recommendations comprises all individuals aged ≥2 years, which is compatible with the NuAge target sample of generally healthy older adults from the greater Montreal, Sherbrooke, and Laval areas of the province of Quebec, Canada.

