### Target Trial

The target trial framework has been suggested as a potential solution to improve the analysis of nutritional epidemiology studies aiming at causal inference [13]. Informally, the target trial framework helps to align the observational data analysis with that of a hypothetical trial. This framework is appropriate for the research question in this study, as we aim to estimate the effect of adhering to a hypothetical diet and physical activity intervention using observational data. The first step of a target trial emulation is the description of the target trial, that is, the protocol for the hypothetical RCT we wish to conduct [11,14]. The second step is the emulation, that is, describing how the target trial is emulated and conducting the study described in this protocol.

Table 1 presents the target trial and its emulation using observational data from NuAge. Key differences between the target trial and its emulation are that participants will be required to provide complete dietary assessment and covariate data at baseline (ie, eligibility component) and that we will attempt to emulate the randomized assignment by adjusting for dietary intakes before baseline as well as baseline covariates (ie, assignment component). Each part of the target trial and its emulation are described in the subsequent sections.

**Table 1 table1:** Emulation of a dietary intervention target trial using observational data from the Quebec Longitudinal Study on Nutrition and Successful Aging (NuAge [25]).

Trial component	Target trial specification	Target trial emulation
Eligibility criteria	NuAge inclusion criteria: individuals aged 67-84 years; living in Montreal, Laval, or Sherbrooke; not cognitively impaired; and free of disabilities in activities of daily living Exclusion criteria: class II heart failure, chronic obstructive pulmonary disease requiring home oxygen therapy or oral steroids, inflammatory digestive diseases, and cancer treatment in the past 5 years	The inclusion and exclusion criteria are the same as those specified in the target trial. Furthermore, participants will be required to have complete baseline dietary assessment (at least one 24-hour recall with ≥500 kcal and FFQ^a^) and provide baseline covariate data.

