**Figure 1 figure1:**
[figure not shown]
Causal directed acyclic graph (DAG) depicting (A) confounding and (B) successful emulation of randomization using g-methods at baseline between the intervention strategy (X) and outcome (Y). Baseline covariates (both time-invariant [Z] and time-varying [L]) and previous diet and physical activity habits (P) must be considered to emulate randomization. Time-varying treatment and covariates are not shown in this DAG to focus on randomization emulation. Subscripts indicate the time points, where 0 represents baseline.

A successful emulation of randomization requires that there is no unmeasured confounding. However, this is never guaranteed with observational data. Thus, we emphasize our assumptions that (1) the causal graph accurately depicts the relationship under study and (2) the covariates included are a sufficient set of covariates to address confounding.

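### The adjustment set names no musculoskeletal or neurological condition, pain or mobility limitation, and its disease list is worded as closed in one place and open in another; taken alone, the omission is expected to favour the activity component of strategy 4 on the primary outcomes, by an amount that may be small

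*Protocol article*

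**What the plan says.** All references are to the protocol article.

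- **Assignment, general list.** The diseases are given as "major chronic diseases (ie, hypertension, diabetes, cancer, and heart disease", a closed wording.
- **Assignment, definition of L (time-varying covariates).** The same four diagnoses appear as "major chronic diseases (eg, hypertension, diabetes, cancer, and heart disease", an open wording. The other members of L begin "weight, number of medications, supplement use, living alone" and end with smoking and alcohol.
- **Assignment, definition of Z.** "baseline covariates: age, sex, region, education, history of smoking, height, and former cancer history". Neither Z nor L contains baseline strength or function.
- **Table 1, eligibility.** "Exclusion criteria: class II heart failure, chronic obstructive pulmonary disease requiring home oxygen therapy or oral steroids, inflammatory digestive diseases, and cancer treatment" (within a five-year window). Inclusion also removes people with cognitive impairment or with disability in daily-living activities. No musculoskeletal or neurological disease is a named exclusion.
- **Outcomes.** The primary outcomes are handgrip, elbow flexor and knee extensor strength, normal and fast walking, and timed up-and-go.
- **Hypothetical Interventions and Table 2.** Strategy 4 adds at least 30 minutes of aerobic activity a day, emulated as a threshold rule.
- **Text below Figure 1.** The protocol assumes that "the covariates included are a sufficient set of covariates to address confounding". The Limitations section counts the derivation of a sufficient set among the study's strengths.
- **Study Design and Sample.** Each annual evaluation covered "functional status, as well as physical and mental health status". The individual items are not listed.

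**The concern.** Arthritis, joint or back pain, a past fracture, a past stroke or early Parkinson disease can each make a person less active and, separately, slower or weaker on the primary tests. Milder forms would pass the eligibility criteria. If no such condition is in the models, the g-formula attributes part of these people's poorer performance to their lower activity, and it predicts too large a gain when activity is raised to the threshold.

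Two features of the design add to the exposure. First, activity is used through time point 3, the visit at which the outcome is read, so a condition that starts between visits 2 and 3 can lower both together. Second, the Assignment section concedes that activity before baseline is not accounted for in the activity models, so earlier habits cannot stand in for the missing condition.

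At stake is the activity half of Hypothesis 2 on the primary outcomes. The argument is made only for that component, not for the diet-only contrasts.

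**Working it through.** **1. Text check.** The plan states no figure on this point, so there is none to reproduce. Set side by side, the covariate lists, the exclusions and the outcomes show that mobility-limiting conditions are neither adjusted for by name nor excluded by name, while every primary outcome is a strength or mobility test. The nearest measured proxies are the number of medications and weight.

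**2. Direction.** Let U be the omitted condition. The bias in the activity coefficient is approximately (effect of U on the outcome) × (slope of U on activity, given the measured covariates). With the outcome scored so that higher is better, both factors are negative and the product is positive, an apparent benefit. For tests recorded as a time, benefit is a shorter time and the sign on the raw scale reverses.

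**3. Size, crude calculation.** All inputs are assumptions: 40% have U; 30% of them and 50% of the others reach 30 min/day; U lowers the test by 0.4 SD.

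- Active share: 0.4 × 0.3 + 0.6 × 0.5 = 0.42.
- P(U given active) = 0.12 / 0.42 = 0.286; P(U given inactive) = 0.28 / 0.58 = 0.483.
- Active minus inactive: 0.4 × (0.483 − 0.286) = 0.079 SD.
- The planned contrast moves only those below the threshold: 0.079 × 0.58 = 0.046 SD.

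Across prevalence 30–50%, active shares 30–40% against 50–55%, and deficits 0.3–0.5 SD, the bias in the planned contrast equals deficit × [P(U) − P(U given active)]:

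- Lowest corner (30%; 40% vs 50%; 0.3 SD): P(U given active) = 0.12 / 0.47 = 0.255, so 0.3 × (0.300 − 0.255) = 0.013 SD.
- Highest corner (50%; 30% vs 55%; 0.5 SD): P(U given active) = 0.15 / 0.425 = 0.353, so 0.5 × (0.500 − 0.353) = 0.074 SD.

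These figures adjust for nothing, and they give everyone below the threshold the active group's mean rather than that of someone at 30 minutes, so they lean high.

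**4. Size, simulation of the threshold rule.** The true activity effect was set to zero, with 400,000 people in each of 24 scenarios. The assumed inputs were: prevalence of U 10, 25 or 40%; outcome deficit 0.2 or 0.5 SD; activity deficit 0.3 or 0.6 SD (mean 35, SD 25 min/day); and a measured proxy correlated 0 or 0.4 with U. A linear model on activity and the proxy was fitted, and activity was then set to the larger of its observed value and 30.

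| Quantity | Range over 24 scenarios |
|---|---|
| Threshold strategy minus natural course, U omitted | +0.001 to +0.027 SD |
| Per 30 min/day, U omitted | +0.006 to +0.090 SD |
| Threshold strategy minus natural course, U included | −0.001 to +0.001 SD |

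The proxy lowered the threshold bias in 9 of 12 paired scenarios. In the other three it rose by less than 0.001 SD, which is within simulation noise. It did not remove the bias.

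**The case against.** **The list may be open.** The definition of L uses *eg*, so a reader who sees only the *ie* list might infer that the adjustment set definitely holds none of these conditions. The document supports less: the list is ambiguous, and neither wording names one.

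**Illness after baseline has its own rule.** The Causal Contrast section lets participants be excused from the strategy when a condition after baseline prevents or limits participation, and says that this reduces confounding by disease burden. This is a partial answer. The rule applies only if such conditions are frequent enough, its examples are major events, and it does not reach conditions already present at time zero.

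**The limitation is disclosed.** The text below Figure 1 and the Discussion both say that freedom from unmeasured confounding is not assured. That caveat is general. It identifies no missing variable and stands beside the assumption that the named set is sufficient.

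**The effect on inference is not shown.** A reader might set the crude active-versus-inactive bias of 0.03 to 0.13 SD against a standard error of 1/√(1300 × 0.42 × 0.58) = 0.056 SD and infer a bias of 0.5 to 2.3 standard errors. The documents do not support this. It is not the planned contrast, it ignores every measured covariate, and the 1300 complete cases and all other inputs are assumptions.

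**The net sign is not fixed.** A reader might also infer that the strategy 4 result is biased toward benefit overall. Activity is self-reported by questionnaire, and the protocol itself accepts that random error in several dietary variables can bias multivariable estimates in any direction. One omitted confounder does not settle the total.

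**Conclusion.** The point stands as a specific gap in the adjustment set. The disease list is worded inconsistently, and neither wording names a condition that limits mobility, although such conditions are plausible common causes of low activity and poor results on the primary tests. Taken alone, the omission is expected to favour the activity component of strategy 4.

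The size cannot be derived from the documents. For the contrast of the threshold strategy with habitual behaviour it is about 0.00 to 0.05 SD: up to 0.027 SD in the simulation and 0.046 SD in the crude base case. Only the extreme unadjusted corner reaches 0.07 SD. These figures rest on assumed prevalence, deficits and activity shares. The eligibility criteria, the medication count and weight would weaken the confounding further. The bias may therefore be small. The reason to act is that the gap is identifiable and inexpensive to close, not that the result is shown to be wrong.

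**What to change.** 1. Use one wording for the disease list and state in full which conditions enter L.
2. Add to L the mobility-limiting conditions that NuAge recorded at baseline and yearly, for example arthritis or joint pain, fracture, stroke and Parkinson disease. Combine rare ones into one or two indicators so that the yearly models stay stable in a sample the protocol itself calls limited. Earlier activity may affect some of these conditions, so they belong among the time-varying covariates, which the g-formula is built to handle.
3. Order them before activity and diet at the same time point, and include them in the incomplete-follow-up model.
4. If the items were not recorded (the article does not say), qualify the sufficiency assumption for strategy 4. Report a quantitative bias analysis for this omitted confounder on the planned contrast, over stated ranges of prevalence and effect, rather than asserting a net direction.

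The cost is a few more covariate models and slightly wider intervals. No new data collection is needed if the items exist.

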**Methods:**

To emulate the target trial, nonexperimental data from the Quebec Longitudinal Study on Nutrition and Successful Aging (NuAge; N=1753 adults aged ≥67 years) will be used. NuAge includes 4 yearly measurements of dietary intakes, covariates, and outcomes. The per-protocol causal contrast will be the primary causal contrast of interest to account for nonadherence. The sustained intervention strategy will be modeled using the parametric g-formula. In the hypothetical trial, participants will be instructed to meet sex-specific minimal intakes for vegetables and fruits, whole grains, animal- and plant-based protein foods, milk and plant-based beverages, and unsaturated fats. The eligibility criteria, follow-up, intervention, outcomes, and causal contrast in the emulation will closely align with those of the target trial, with only minor modifications. We will attempt to emulate the randomization of treatment by adjusting for baseline covariates and prebaseline dietary habits.

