### Outcomes

The primary outcomes will be the mean end of follow-up values for muscle strength (ie, handgrip using vigorimeter, elbow flexor, and knee extensor) and physical function (ie, normal and fast walking and “timed up-and-go”). Outcome values were measured according to a standardized protocol in NuAge [25].

For secondary outcomes, mean end of follow-up values for a set of relevant variables will be considered by domains:

*General health:* waist circumference, blood pressure (systolic and diastolic), blood glucose, and estimated glomerular filtration rate*Cognition:* the modified Mini-Mental State Examination score

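### The listed adjustment sets contain no baseline or interim outcome value, which leaves plausible residual confounding by prior strength and function and gives up precision

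*Protocol article*

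**What the plan says.** The Assignment section gives the adjustment variables node by node.

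- Z: "baseline covariates: age, sex, region, education, history of smoking, height, and former cancer history".
- P: "previous exposure (ie, exposure of time-varying intervention before baseline): dietary habits before baseline".
- L: "weight, number of medications, supplement use, living alone, major chronic diseases (eg, hypertension, diabetes, cancer, and heart disease), and smoking and alcohol habits".
- Y: "end of follow-up outcome: muscle health, general health, and cognitive health".

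The Eligibility Criteria section requires complete baseline data on the covariates identified in Assignment, so the list is operative. The text under Figure 1 assumes that the listed covariates suffice to deal with confounding, and the Limitations section counts this among the strengths.

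On the outcomes, the Outcomes section specifies "mean end of follow-up values for muscle strength" and likewise for physical function, so the target is a final level. On availability, the Abstract states "NuAge includes 4 yearly measurements of dietary intakes, covariates, and outcomes", and Study Design and Sample states that "each annual follow-up evaluation included a comprehensive assessment of sociodemographic data, diet, physical activity, functional status" and more. Assignment also says that activity habits before baseline were not collected and cannot be adjusted for in the physical activity strategy.

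**The concern.** A participant's strength, gait and mobility at one visit are likely to influence what that person eats and how much they move afterwards, and they strongly predict strength and gait at year 3. If so, prior function is a common cause of exposure and outcome at every time point. Because the outcome is a level, differences between people that already exist at time zero are not removed by the outcome definition. Any part of them that the listed covariates do not explain can appear as an effect of the strategy.

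The physical activity strategy is the most exposed. Activity before baseline is not available, and baseline function is the most direct measured variable that could carry part of its influence. Precision is also at stake, since the earlier value of a stable measure is usually the best single predictor of the later one, and the protocol itself calls its sample of 1753 relatively limited.

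**Working it through.** The protocol states no power, precision or bias figure, so there is nothing of its own to reproduce.

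**Step 1: is the variable in any set?** Reading Z, P and L item by item, none contains handgrip, elbow or knee strength, walking speed, timed up-and-go, the cognitive score, waist circumference, blood pressure, glucose or filtration rate. Y is defined at the end of follow-up only. No other section adds an earlier outcome value.

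**Step 2: what partial proxies are present?** Age, sex, height, weight, medication count and chronic disease correlate with strength and gait. Prior-year diet absorbs part of any stable link between function and diet. Hypertension, diabetes and weight are coarse markers for some secondary outcomes. The diet-only models adjust for physical activity during the study. Eligibility removes people with disability in daily living and with cognitive impairment. These narrow the gap, but none measures strength or gait.

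**Step 3: precision.** Let r be the correlation between the baseline and year-3 outcome (assumed; not in the document). Adjusting for the baseline value multiplies residual variance by 1 − r² and the standard error by √(1 − r²). The equivalent sample size is 1753/(1 − r²).

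| r | 1 − r² | SE ratio | Equivalent N |
|---|---|---|---|
| 0.5 | 0.75 | 0.87 | 2337 |
| 0.6 | 0.64 | 0.80 | 2739 |
| 0.7 | 0.51 | 0.71 | 3437 |
| 0.8 | 0.36 | 0.60 | 4869 |

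These are best cases. The existing covariates already explain part of the variance, so the true gain is smaller.

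**Step 4: direction of bias, illustration only.** A simulation set the true effect to zero. Year-to-year outcome correlation was 0.8 to 0.9, the exposure at each visit correlated g with current function, and one measured proxy correlated 0.3 to 0.5 with baseline function. Year-3 outcome was regressed on exposure at time points 0 to 2 and the proxy (400,000 records). The entries are the spurious effect, in outcome SD, of an exposure raised by 1 SD at all three time points.

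| g | No earlier outcome | Baseline value added | Baseline, years 1 and 2 added |
|---|---|---|---|
| 0 | about 0 | about 0 | about 0 |
| 0.1 | 0.16 to 0.22 | 0.05 to 0.07 | about 0 |
| 0.2 | 0.32 to 0.43 | 0.09 to 0.15 | about 0 |
| 0.3 | 0.45 to 0.60 | 0.15 to 0.22 | about 0 |

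If current function does not influence exposure (g = 0), no bias arises and only precision is lost. Otherwise the baseline value removes most of the bias in these runs or somewhat more than half of it, and the interim values are needed for the rest. The simulation omits prior diet and most of the planned covariates, and it is per SD of exposure rather than for the threshold strategies of Table 2. It shows the mechanism and does not estimate the bias in this study.

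**The case against.** The case on the other side has real substance.

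- **Proxies exist.** A reader might infer that nothing in the list stands in for function. Step 2 shows otherwise. Under Causal Contrast, participants with major health events may also be excused from the strategy, if such events are frequent enough. This aims at confounding by disease burden, although it does not cover gradual loss of strength.
- **The bias is not quantified.** A reader might infer that the primary contrasts are biased by some stated fraction of an SD. The document gives neither the outcome correlation nor the link between exposure and function that remains after adjustment, so no such figure is supported.
- **Dropout.** A reader might infer that the handling of incomplete follow-up is invalid. Table 1 defines that adjustment by a criterion, namely factors associated with adherence and with incomplete follow-up. The criterion does not exclude prior function, and no dropout pattern is reported. Invalidity is not shown.
- **Availability.** The statements on yearly measurement are general and do not confirm that every test was done at time points 1 and 2.
- **Condensed article.** Outcome-specific terms are often left to a full analysis plan, and the two causal diagrams are missing from the text reviewed. However, the article sorts its covariates explicitly, ties eligibility to them and assumes that they suffice. The omission is therefore a stated choice and not just missing detail.

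The first four points limit the size and certainty of the concern. They do not remove it for the primary outcomes.

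Over-adjustment is not a good defence. The strategy starts at baseline, so the time point 0 outcome serves as pre-strategy information. Later values are both confounders and mediators, and the protocol chose the g-formula to handle exactly that kind of feedback.

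**Conclusion.** The concern holds in a limited form. The adjustment sets contain no earlier outcome value, although the cohort is described as measuring outcomes and functional status yearly and the primary outcomes are final levels. Residual confounding by prior strength and function is plausible, and most clearly so for the strategy that includes physical activity. It depends on prior function influencing diet or activity beyond what the listed covariates capture, and its size cannot be computed from the document.

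The precision loss does not need that condition. It needs only an outcome that correlates with its own baseline beyond the existing covariates. Under an assumed correlation of 0.5 to 0.8, the standard error ratio of 0.87 to 0.60 is a ceiling on the gain.

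**What to change.** 1. Add the time point 0 value of the outcome being analysed to the baseline covariates, in both the per-protocol and the intention-to-treat analyses and in the models for incomplete follow-up.
2. In the per-protocol g-formula only, add the time point 1 and 2 values to L where they were measured, each modelled as a time-varying confounder.
3. Do not enter the time point 1 and 2 values in the intention-to-treat outcome regression. That analysis concerns a point intervention at baseline, and adjusting for later values would remove part of the effect it aims to estimate.
4. Update Figures 1 and 2 to show the earlier outcome values.
5. State in Time Zero and Follow-Up whether a missed interim test counts as incomplete follow-up. As written, a missing covariate is carried forward once and the participant then counts as incomplete, so placing tests in L could turn repeatedly missed tests into censoring.

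If the general statement on yearly measurement holds, no new data are needed. The costs are that participants without a baseline test leave that outcome's analysis, and that each interim value needs its own model, with some added risk of misspecification in a modest sample. The number lost cannot be read from the document and should be reported by outcome.
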